### Documentation

Investigation of AEs is part of every assessment of the study participants. Any AE has to be documented in the CRF.

Every SAE has to be documented on a special documentation form and has to be reported within 24 hours after recording, but at least at the next working day, to the data monitoring center in Berlin.

### Statistical Analysis

All data are described according to their mean, median or frequency, as applicable. The dichotomized modified Rankin score as primary outcome variable is investigated in using univariate analysis. Multivariate logistic regression modeling is performed accordingly, adjusted for clinical grade, fisher grade, ventricular hemorrhage, parenchymal hemorrhage, gender, nimodipine or other concomitant medical treatment. Analysis is planned as intention-to-treat as well as per protocol, excluding the patients who were treated with amounts of CSF drainage via lumbar drain deviating from the specified 5 ml/h or which needed a lumbar drain when randomized to the No-LD group.

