### Randomization

Any patient meeting the inclusion criteria and not violating the exclusion criteria may participate in the EARLYDRAIN study and be randomized to either receive a lumbar drain or not, thus defining the two distinct groups LD and NoLD.

Randomization is performed via a dedicated internet site accessible for all local investigators of the participating trial centers http://www.randomizer.at. No stratification or minimisation is to be used. The security measures of the online randomization system "randomizer.at" include that 1. All transactions are logged, 2. The audit trail of the trial can be accessed and analysed any time by the trial monitoring committee. 3. Network traffic between the web-browser and the randomizer is encrypted using SSL (*Secure Sockets Layer*) with strong encryption.

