To assess a decrease of the incidence of DND from 40% to 20% in a prospective clinical trial, 93 patients in each of the two study arms are required to gain a power of 85%, using an alpha error of 5%. To account for possible imbalances in the randomization procedure concerning severity of clinical and radiological grading of the SAH or the choice of treatment and to facilitate a preplanned analysis on the severity of the initial hemorrhage, the planned study size is to include and randomize altogether 300 patients. This results in a power of 85.2%, again, using an alpha error of 5%, to detect a decrease in the rate of severe disability on a dichotomized modified Rankin scale from 50% to 33%, which would be consistent with the effect size from the retrospective trials on a dichotomized GOS [12,13]. The EARLYDRAIN investigators are aware of other, more conservative calculations for the sample size of patient-centered outcome studies targeting vasospasm, indicating that there may be the necessity to include more than 5000 patients in a single trial [17]. The power calculations, as described above and based on the available retrospective data, do not substantiate numbers this large. Besides feasibility issues, clinical experience from the principal investigators considering the expected effort-benefit ratio does not warrant enlargement of the trial to detect a rather small difference between groups.

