### Outcome assessment

The primary endpoint is disability after 6 months, assessed by the modified Rankin Scale [18] dichotomized at a score of 0 to 2 versus 3 to 6 (6 = death). Assessment is performed by a blinded investigator of the local study center by personal visit. Alternatively, a telephone questionnaire is suitable for outcome assessment using the modified Rankin Scale [19]. Outcome assessment is planned to be done on the whole dataset as well as in preplanned stratified subsets (i.e. for example clinical SAH grade according to the Hunt&Hess scale 1-2 vs. 3-5 [20], CT grading according to Fisher I-III vs. IV [21]).

Secondary outcome criteria are:

• Mortality after 6 months

• mRS score after 6 months as continuous variable

• Angiographic vasospasm on day 7 to 10, as defined by a caliber reduction by 33% or more compared to the initial digital subtraction angiography

• Endovascular rescue therapy performed due to proven vasospasm, using balloon dilation of spastic vessels and/or arterial infusion of vasodilators

• Infarction (due to vasospasm) in the last CT scan before discharge

• Expression of clinical delayed neurological deficit after the aneurysmal SAH until discharge from acute care.

• Daily course of TCD mean flow velocity in both MCA at a depth of 50-60 mm

• Rate of death during the initial hospital treatment after the aneurysmal SAH.

• Rate of CSF shunt insertion during the first six months

• Presence of CSF infection during the first 14 days, as defined by modified CDC criteria for device-associated meningitis (treatment required on either positive culture, or elevated cell count, red cell/white cell ratio, increased lactate and/or decreased glucose) [22].

The following parameters will be recorded and used in predictor-/association models concerning primary and/or secondary outcome parameters:

• Gender

• Age

• Hunt&Hess grade on admission

• Time from symptom onset to admission

• Location of aneurysm

• Time from symptom onset to aneurysm treatment

• Treatment of aneurysm by clipping or coiling or both

• Time from symptom onset to randomization

• Time from symptom onset to treatment start (i.e. insertion of the lumbar drainage in the treatment arm)

• Time from admission to discharge

• Insertion of EVD (yes/no)

• Duration of EVD being in place

• Duration of lumbar drainage

• Amount of CSF drained by EVD [ml]

• Amount of CSF drained by lumbar drain [ml]

• Use of nimodipine (yes/no)

• Use of statins (yes/no)

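### The plan foresees chance imbalance in SAH grade and aneurysm treatment, yet leaves the primary comparison unadjusted and the supporting model without age and clip/coil: a valid test, but precision forgone

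*Protocol article*

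**What the plan says.** Four parts of the protocol article bear on this point.

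- **Sample size calculation.** One reason given for the larger trial reads: "To account for possible imbalances in the randomization procedure concerning severity of clinical and radiological grading of the SAH or the choice of treatment". Another is a planned analysis by severity of bleeding. The outcome is that "the planned study size is to include and randomize altogether 300 patients". The stated power at that size is 85.2% for 50% versus 33% with severe disability, at an alpha of 5%.
- **Randomization.** "No stratification or minimisation is to be used".
- **Statistical Analysis.** "The dichotomized modified Rankin score as primary outcome variable is investigated in using univariate analysis". A multivariable logistic model accompanies it, "adjusted for clinical grade, fisher grade, ventricular hemorrhage, parenchymal hemorrhage, gender, nimodipine or other concomitant medical treatment". The section does not say in words which of the two results decides.
- **Outcome assessment and Interventions.** The primary endpoint is the 6-month mRS, 0-2 versus 3-6. Age and treatment by clipping or coiling are both recorded, but appear only among parameters for predictor or association models. Randomisation follows securing of the aneurysm, so both are fixed by then.

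**The concern.** The plan names a risk and then sets aside both direct remedies in the analysis that carries the trial. Stratification is excluded at randomisation, and a univariate comparison cannot adjust. A larger sample narrows the expected imbalance but does not correct the imbalance that occurs in the one trial run.

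The supporting model fills the gap only in part. It includes clinical and Fisher grade. It leaves out clip/coil, although choice of treatment is one of the imbalances the sample size section worries about, and it leaves out age. It does include nimodipine or other concomitant treatment, which is open-ended and may be given after randomisation. A covariate that treatment can influence can distort the estimated treatment effect.

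At stake are the precision of the primary result and how easily it can be read if the arms differ in grade.

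**Working it through.** **1. Which analysis was the trial sized for?** Inputs: 50% and 33%, total 300, alpha 5% (Sample size calculation). Assumed: 150 per arm and a two-sided test, since neither is stated.

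- Mean rate = 0.415; SE under the null = sqrt(2 × 0.415 × 0.585 / 150) = 0.0569.
- SE under the alternative = sqrt((0.50 × 0.50 + 0.33 × 0.67) / 150) = 0.0560.
- Power = Φ((0.17 − 1.96 × 0.0569) / 0.0560) = Φ(1.04) = 85.17%.

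This reproduces the stated 85.2% with an unadjusted comparison, which supports reading the univariate test as the deciding one. The same method returns 93 per arm for 40% versus 20% at 85% power, also as stated. Solving for 85.2% at 50% versus 33% gives 151 per arm. On the primary endpoint, then, the 300 patients are fully used and leave no separate allowance for imbalance.

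**2. How much does enlargement reduce imbalance?** The SD of the arm difference in the share of poor-grade patients is sqrt(2 × s × (1 − s) / n). The share s is not in the article; 30% and 50% are assumed.

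| s | n per arm | SD (points) | 95% range | chance of a gap above 10 points |
|---|---|---|---|---|
| 50% | 93 | 7.3 | ±14.4 | – |
| 50% | 150 | 5.8 | ±11.3 | 8.3% |
| 30% | 150 | 5.3 | ±10.4 | 5.9% |

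**3. What would a 10-point gap do to the crude result?** Assume half the patients are poor grade, 50% have a poor outcome overall, and grade acts alone. The outcome gap between grades is then (√OR − 1)/(√OR + 1).

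- OR 3: 0.732 / 2.732 = 0.27, a shift of 0.10 × 0.27 = 2.7 points.
- OR 8: 1.828 / 3.828 = 0.48, a shift of 0.10 × 0.48 = 4.8 points.

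That is about 3 to 5 points against a planned difference of 17.

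**4. What does adjustment gain?** Logistic regression was simulated with 150 per arm, half poor grade and marginal rates held at 50% and 33%. There were 3,000 runs per row, with Monte Carlo error of about 0.6 points.

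| Assumed OR, grade | Assumed OR per SD, age | Crude | Adjusted: grade | Adjusted: grade and age |
|---|---|---|---|---|
| 1 | 1 | 85% | 85% | 85% |
| 3 | 1.5 | 85% | 87% | 88% |
| 5 | 1.5 | 86% | 90% | 90% |
| 5 | 2 | 85% | 88% | 91% |
| 8 | 2 | 86% | 91% | 93% |

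The gain from grade and age is about 3 to 8 points. For scale, a crude test needs 175 per arm, 350 in total, for 90% power. The effect of adding clip/coil was not simulated.

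**5. Is the crude test sound?** Under no treatment effect (grade OR 5, age OR 2, 4,000 runs) it rejects in 5.0% of trials. The adjusted tests reject in 5.2% and 5.3%.

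**The case against.** The strongest defence is that nothing here is invalid. Chance imbalance is already part of the crude standard error. The 95% half-width at the planned rates is 1.96 × 5.6 = 11 points, and a 3 to 5 point shift lies well inside it. Type I error holds and the planned power is met. An adjusted model covering clinical grade, Fisher grade and both hemorrhage types is already planned. Age and clip/coil are earmarked for other models, and an analysis plan not shown here may settle the covariate list. Most of this stands, and it limits the point to efficiency and interpretation. It does not remove the point, because the univariate analysis and the covariate list are choices the article states, not details it leaves open.

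A reader might infer more in three ways that the documents do not support.

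- **Inflated type I error from two tests.** The ranking is not written out, but the power calculation identifies the crude test, and nothing says that either result may be claimed. Simulations of that hypothetical rule gave about 6.6% to 7.7% under assumed covariate effects. The figure does not describe this plan.
- **Grade imbalance persists because age and clip/coil are missing.** It persists in the primary result because that result is crude. The two omissions are a separate weakness of the supporting model.
- **Stratification should be switched on mid-trial.** Changing the allocation scheme during recruitment is debatable, and adjustment in the analysis makes it unnecessary.

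**Conclusion.** The point holds as a worthwhile improvement. The article identifies imbalance in grade and choice of treatment as a risk, yet its deciding analysis corrects for neither, and its supporting model omits the second as well as age. The cost is forgone precision, not a biased test or a shortfall against the stated 85.2%.

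The size rests on assumptions, because the article gives no prognostic strength and no grade distribution. Across the ranges used, power would rise from about 85-86% to 88-93%, and there is no gain if the covariates carry no prognostic information. A grade gap large enough to move the crude difference by 3 to 5 points would occur in roughly one trial in 12 to 17 (8.3% to 5.9%).

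**What to change.** Before unblinding, amend the Statistical Analysis section as follows.

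- Name one primary analysis: an intention-to-treat logistic regression of the dichotomised 6-month mRS on treatment arm and prespecified baseline covariates. These are age, Hunt&Hess grade, Fisher grade, ventricular hemorrhage, parenchymal hemorrhage, gender and clip/coil.
- State that grading and hemorrhage covariates come from assessments made before randomisation.
- Report a standardised risk difference with its confidence interval, next to the odds ratio.
- Keep the crude comparison as supportive.
- Take nimodipine and other concomitant treatment out of this model.

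At the planned rates about 150 × 0.50 + 150 × 0.33 = 124.5 poor outcomes are expected, roughly 15 per term for treatment plus seven single-term covariates (124.5 / 8).

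The cost is protocol or analysis plan wording. No extra patients are needed, and age and clip/coil are already collected. The drawback is that a conditional odds ratio is slightly harder to explain than a crude one, which the standardised risk difference addresses. The randomisation procedure can stay as it is.

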After cerebrovascular imaging on day 7 to 10 the lumbar drainage of CSF is stopped in the LD-group. If cerebrovascular imaging is carried out before day 7, lumbar drainage is stopped on day 8. It may be pursued on a clinical base, as required.

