### Amount and duration of CSF drainage

Patients randomized to the lumbar drainage group shall receive a daily drainage of 120 ml CSF, or 5 ml per hour for seven days. If higher amounts of CSF need to be drained on clinical grounds as in patients with hydrocephalus, this is preferably performed via an external ventricular drain.

The drain is planned to remain in place until the control angiography on day 7 to 10 after the initial hemorrhage. The local investigator may decide to remove the drain earlier in patients fully mobilized without clinical necessity of CSF drainage. However, consecutive drainage should not be less than four days to achieve a valid study result. Lumbar CSF drainage may be prolonged beyond the control angiography on clinical requirement. The amount of CSF drainage may then be adjusted to clinical requirements and bears no further restriction.

Patients randomized to the control group should not receive a lumbar drain before the planned control angiography to be performed on day 7 to 10 after SAH. If the patient develops hydrocephalus, and no EVD was placed initially for CSF drainage, a lumbar drain may be installed at the discretion of the local investigator. These patients are analyzed in the intention-to-treat analysis, but are not suitable for the per-protocol analysis.

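### The per-protocol exclusions have no time limit, although the protocol restricts lumbar drainage only up to the day 7 to 10 angiography; the conflict is clearest for controls

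*Protocol article*

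**What the plan says.** The Protocol article plans a per-protocol analysis alongside intention-to-treat. Under Statistical Analysis it is formed by "excluding the patients who were treated with amounts of CSF drainage via lumbar drain deviating from the specified 5 ml/h". The control arm has its own clause, which removes patients by these words: "or which needed a lumbar drain when randomized to the No-LD group". No day or period is attached to either clause.

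The section Amount and duration of CSF drainage sets the rules these clauses are meant to enforce, and there they are tied to time:

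- Lumbar-drain arm, dose: "Patients randomized to the lumbar drainage group shall receive a daily drainage of 120 ml CSF, or 5 ml per hour for seven days".
- Lumbar-drain arm, after imaging: "Lumbar CSF drainage may be prolonged beyond the control angiography on clinical requirement", and "The amount of CSF drainage may then be adjusted to clinical requirements and bears no further restriction". The last paragraph of Interventions also allows continuation after the planned stop: "It may be pursued on a clinical base, as required".
- Control arm: "Patients randomized to the control group should not receive a lumbar drain before the planned control angiography to be performed on day 7 to 10". The same paragraph then allows a lumbar drain for hydrocephalus where no ventricular drain was placed initially, and says such patients do not belong in the per-protocol analysis. That sentence gives no day of its own.

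**The concern.** A per-protocol set should contain the patients who followed the protocol. Here the exclusion rule runs on without an end, while the treatment rule behind it stops at the imaging. A patient can therefore comply with the treatment section and still be removed by the analysis section.

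Late lumbar drainage is not random. The protocol ties it to clinical requirement, so it marks patients who still need cerebrospinal fluid diversion after the first week or so. Removing them selects on something that happens after randomization. The two arms also have different triggers: a control leaves for needing any lumbar drain, whereas a lumbar-drain patient leaves only if the amount departs from 5 ml/h. If late need is related to the six-month modified Rankin score, the two per-protocol groups may no longer be comparable. Two analysts working from this text could also build different per-protocol sets.

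**Working it through.** **1. The sections side by side**

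| Patient | Amount and duration of CSF drainage | Statistical Analysis, as written |
|---|---|---|
| Lumbar-drain arm, 5 ml/h to imaging, then stopped | Compliant | Kept |
| Lumbar-drain arm, 5 ml/h to imaging, prolonged at 5 ml/h | Compliant, expressly allowed | Kept |
| Lumbar-drain arm, 5 ml/h to imaging, then another rate | Compliant, expressly allowed | Excluded literally; kept if the seven days are read in |
| Control, lumbar drain before the planned angiography | Restricted; hydrocephalus exception declared outside per-protocol | Excluded, consistent |
| Control, first lumbar drain after that point | No longer forbidden | Excluded |

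The last row is the clear conflict. The third row depends on the reading. Even on the milder reading the two clauses end on different clocks: seven days, presumably counted from the start of drainage, in one arm, and an angiography dated from the hemorrhage in the other.

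**2. The plan's own figure, as a yardstick**

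The planned effect on the dichotomized modified Rankin scale is 50% versus 33%, or 17 points. With 150 per arm (1:1 assumed) and two-sided 5%, the pooled-variance formula gives

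z = [0.17·√150 − 1.96·√(2·0.415·0.585)] / √(0.50·0.50 + 0.33·0.67) = (2.082 − 1.366)/0.686 = 1.04, so power is 85.2%, as stated. The point at issue does not touch this figure.

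**3. What selection could do, on assumed rates only**

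The protocol gives no rate of late drainage and no outcome rate in such patients. Assume no true effect and a 50% poor outcome in each arm.

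*Case A: more controls removed.* A share q of each arm has late need, and 70% of these have a poor outcome. All such controls are dropped, and a share k of such lumbar-drain patients stays at 5 ml/h and is kept.

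- Control rate = (0.50 − 0.70q)/(1 − q)
- Lumbar-drain rate = (0.50 − 0.70q + 0.70kq)/(1 − q + kq)

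| q | Control | Lumbar drain, k = 0.5 | Difference | Lumbar drain, k = 1 | Difference |
|---|---|---|---|---|---|
| 10% | 0.4778 | 0.4895 | 0.0117 | 0.5000 | 0.0222 |
| 20% | 0.4500 | 0.4778 | 0.0278 | 0.5000 | 0.0500 |
| 30% | 0.4143 | 0.4647 | 0.0504 | 0.5000 | 0.0857 |

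That is 1.2 to 8.6 points against drainage.

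*Case B: more lumbar-drain patients removed.* Thirty percent of the lumbar-drain arm and 10% of controls are lost. With share x lost and poor-outcome rate r among the lost, the remaining rate is (0.50 − x·r)/(1 − x).

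- r = 60%: 0.32/0.70 = 0.457 versus 0.44/0.90 = 0.489, or 3.2 points in favor of drainage.
- r = 70%: 0.29/0.70 = 0.414 versus 0.43/0.90 = 0.478, or 6.3 points in favor.
- Equal losses of 20% with r = 70%: 0.36/0.80 = 0.450 in both arms, so no bias.

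**The case against.** The strongest reply is that the sections can be read consistently. The analysis section refers to a specified rate, and that specification includes seven days; once the amount is unrestricted, there is nothing left to deviate from. The control paragraph first bars drains before the angiography and then gives the hydrocephalus exception, so its per-protocol sentence may concern only early drains, with the analysis section as a short summary of it. For the lumbar-drain arm this reading is plausible, and a reader who infers that a late rate change certainly excludes a patient goes further than the text. For controls the reply is weaker, because the analysis clause names any need for a lumbar drain and the hydrocephalus sentence is undated.

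A reader might also infer that the protocol expressly permits late drains in controls. It does not: the permission is express in the lumbar-drain arm, while for controls the restriction simply ends.

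Different triggers are not in themselves an error. The assigned treatments differ, so adherence must be judged differently while they apply. What lacks an adherence rationale is carrying the triggers past the period in which they apply.

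The illustration has limits too. Case A assumes that everyone with late need gets a lumbar drain, although ventricular drainage is allowed in both arms and is preferred for higher amounts. With k = 1, no late rate change occurs at all.

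Finally, detail of the per-protocol set may sit in an analysis plan that is not shown. That would answer a complaint about missing detail, but not one about a printed rule that, for controls, disagrees with the treatment section.

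**Conclusion.** The point holds as a conflict of wording with consequences for the per-protocol set. It is clear for controls first drained after the planned angiography, and a matter of ambiguity for lumbar-drain patients whose rate changes later. Both exclusions depend on need after randomization and can act differently by arm.

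The bias cannot be sized or signed from the document. It would be tempting to conclude that the per-protocol result is biased against drainage by several points of the planned 17. The document does not support this: the rates are assumed, and the direction turns on which arm loses more patients. A particular effect on shunt insertion is conceivable, but no figure supports it. The intention-to-treat analysis and the sample size are not affected, so this is a repair worth making and not a threat to the main analysis.

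**What to change.** Reconcile Statistical Analysis with Interventions and with Amount and duration of CSF drainage:

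- Limit both per-protocol exclusions to the period in which the protocol restricts lumbar drainage.
- Define the end of that period, for analysis only, as one cut-off day after the hemorrhage that is the same in both arms. It must also cover patients imaged before day 7 and those whose imaging is omitted, both of which the protocol foresees. A cut-off tied to each patient's own imaging would leave these cases open.
- State that lumbar drainage after that day, in either arm and at any rate, does not remove a patient from the per-protocol set.

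The trial team should choose the day before outcome data by arm are seen. Nothing in patient care changes.

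The cost is a sentence or two of text and a check of the case report form. Start and stop dates of lumbar drains are needed in both arms, and amounts must be separable before and after the cut-off. The article lists duration and amount of lumbar drainage, but gives time to insertion only for the treatment arm, so dates for controls in particular need confirming.

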**Figure 1 F1:**
[figure not shown]
**EARLYDRAIN study algorithm**. The EARLYDRAIN study algorithm showing the course of events after the initial aneurysmal subarachnoid hemorrhage (SAH) and the subsequent surgical or interventional aneurysm treatment. The study includes two groups, a treatment group receiving lumbar CSF-drainage (LD) and a control group receiving no lumbar drainage according to protocol (NoLD). The timing of the patient's consent to study participation, randomization, cranial imaging and assessment of clinical outcome is indicated by the shaded boxes. Imaging on day 7 to 10 is scheduled according to local guidelines. If a local center performs no routine cerebrovascular imaging for vasospasm screening in patients without clinical suspicion, it may be omitted.

In patients in the LD-group, CSF drainage via the lumbar drain is started slowly and steadily at a rate of approximately 5 ml per hour after the post-interventional CCT. This leads to a planned daily CSF-drainage of 120 ml per day through the lumbar route. Patients in both groups may receive additional CSF drainage via a ventricular device. The amount of CSF drained via the ventricular route is determined according to clinical requirement and not specified by the study protocol.

In order to enhance accuracy of the amount of CSF drained, regular drainage control every other hour and stopping in case of excess drainage is strongly recommended by the principal investigators. In case of neurological decline suspiciously related to the lumbar drainage, the drain must be closed immediately. Drainage may be gradually restarted after 12 to 24 hours, after performing a CCT scan.

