If the post-procedural CCT or any other follow-up CCT scan shows compressed basal cisterns or any signs of threatening herniation, lumbar CSF diversion in the LD-group must not be performed. It may still be feasible to carefully drain CSF via the lumbar route [14], but this is at the discretion of the local investigator and not recommended. In patients requiring sedation and mechanical ventilation, either due to neurological impairment or for other medical reasons, intracranial pressure monitoring is mandatory. This may be performed according to local policy either with parenchymal or ventricular devices. If the intracranial pressure exceeds 20 mmHg, further CSF drainage via lumbar route shall be interrupted until the ICP is below 20 mmHg again. Careful CSF-drainage via the lumbar route may still be feasible in case of high intracranial pressure [14], but again this is at the discretion of the local investigator. A method of detecting the safety of lumbar CSF diversion may be determining the gradient of lumbar versus intracranial CSF pressure [15]. Albeit promising, the Earlydrain investigators explicitly rate this approach preliminary and experimental. In case of doubt, lumbar CSF diversion must not be performed.

Further neuromonitoring with transcranial duplex sonography (TCD), electroencephalography (EEG), brain tissue oxygenation recordings, jugular bulb oxymetry, regional cerebral blood flow measurement, microdialysis or other methods is at the discretion of the center and according to its local guidelines. As far as possible, this data should be saved electronically for post-hoc analysis.

A CCT scan as well as conventional digital subtraction angiography (DSA), CT angiography or MR angiography for assessment of vasospasm in the larger vessels is routinely performed on day 7 to 10 after the initial hemorrhage, according to local guidelines. In case of the occurrence of a DND when vasospasm is assumed to be the cause, angiography may be performed at any time. If it is performed earlier than day 7 to 10 and the patient shows no clinical deterioration thereafter, the angiography on day 7 to 10 is omitted. Treatment of radiographically confirmed vasospasm is according to local guidelines and not specified in the Earlydrain study protocol. It may include augmentation of cerebral blood flow via hypertensive hypervolemia as well as endovascular balloon dilation or intraarterial infusion of vasodilators.

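### The per-protocol set excludes lumbar-drain patients whose drainage was stopped because the protocol required it, which probably tilts that analysis towards drainage; ITT is unaffected but is not named as deciding

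*Protocol article*

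**What the plan says.** The Statistical Analysis section plans two analysis sets: "Analysis is planned as intention-to-treat as well as per protocol". The per-protocol set is formed by "excluding the patients who were treated with amounts of CSF drainage via lumbar drain deviating from the specified 5 ml/h", and the same sentence goes on to remove controls: "or which needed a lumbar drain when randomized to the No-LD group".

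The section on amount and duration of CSF drainage says who those controls are: patients who develop hydrocephalus, had no EVD at the start, and then receive a lumbar drain. Of them it says: "These patients are analyzed in the intention-to-treat analysis, but are not suitable for the per-protocol analysis".

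The Interventions section (text after Figure 1) contains three rules that take a drainage-arm patient off the target rate:

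- Decline thought to be due to the drain: "In case of neurological decline suspiciously related to the lumbar drainage, the drain must be closed immediately". A gradual restart is possible after 12 to 24 hours.
- ICP above 20 mmHg: "further CSF drainage via lumbar route shall be interrupted until the ICP is below 20 mmHg again".
- Compressed basal cisterns or signs of threatening herniation on a CCT: "lumbar CSF diversion in the LD-group must not be performed".

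That section gives the target rate only as approximate. The section on amount and duration also lets the local investigator remove the drain early in fully mobilised patients, while asking for at least four days of drainage for a valid result.

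**The concern.** A per-protocol set is meant to hold patients treated as the protocol prescribes. Here the definition and the treatment rules disagree: a drain closed because the protocol orders it is a departure from 5 ml/h, and nothing in the definition exempts it.

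The excluded patients are unlikely to be a random sample of their arm. Raised ICP, compressed cisterns and neurological decline arise after randomisation and plausibly mark severe brain injury. The decline rule also picks out patients whom the drain itself may have harmed. A control with the same ICP or CCT finding has no lumbar rate to deviate from and stays in. The per-protocol comparison can therefore lose poor-prognosis patients, and possible harm, from the drainage arm while keeping their counterparts among controls.

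This matters most because the two analyses are listed together without a ranking. If they disagree on the primary endpoint, the article does not say which one answers the trial's question.

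**Working it through.** **The plan's own figure.** The sample size section states 85.2% power with 300 patients for 50% against 33% on the dichotomised mRS at alpha 5%. Take 150 per arm (1:1 is assumed; no ratio is stated), two-sided, pooled variance under the null:

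- mean rate 0.415; s0 = √(2 × 0.415 × 0.585 / 150) = 0.0569
- s1 = √((0.25 + 0.2211) / 150) = 0.0560
- power = Φ((0.17 − 1.96 × 0.0569) / 0.0560) = Φ(1.04) = 85.2%

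The figure reproduces with all 300 randomised patients. The plan gives no figure for the per-protocol set.

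**Inputs for the bias check.** The poor-outcome rate (mRS 3–6) is 50% in both arms, meaning no effect; 50% is the plan's control rate. The share *f* of the drainage arm excluded and its poor-outcome rate *q* are assumptions; the documents give neither. For controls the corresponding assumed values are *g* and *r*.

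**Formulas.** Retained drainage-arm rate p1 = (0.50 − f·q)/(1 − f); retained control rate p2 = (0.50 − g·r)/(1 − g); spurious benefit D = p2 − p1. With s0 the pooled and s1 the unpooled standard error at the retained sizes, the two-sided false-positive rate is Φ((D − 1.96·s0)/s1) + Φ((−D − 1.96·s0)/s1).

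**Worked case, f = 20%, q = 70%, no control exclusions.** p1 = (0.50 − 0.14)/0.80 = 0.450, on 120 patients; p2 = 0.500, on 150. D = 5.0 points, s0 = 0.0612, s1 = 0.0611. Rate = Φ(−1.14) + Φ(−2.78) = 12.9%. A simulation of 200,000 trials gave 13.1%.

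| Drainage arm excluded (f, q) | Controls excluded (g, r) | Drainage vs control, % poor | Spurious benefit (points) | False-positive rate |
|---|---|---|---|---|
| any f, 50% | none | 50.0 vs 50.0 | 0 | 5.0% |
| 10%, 70% | none | 47.8 vs 50.0 | 2.2 | 6.6% |
| 20%, 70% | none | 45.0 vs 50.0 | 5.0 | 12.9% |
| 30%, 70% | none | 41.4 vs 50.0 | 8.6 | 27.0% |
| 25%, 80% | none | 40.0 vs 50.0 | 10.0 | about 36% |
| 25%, 80% | 10%, 60% | 40.0 vs 48.9 | 8.9 | about 29% |
| 20%, 70% | 10%, 60% | 45.0 vs 48.9 | 3.9 | 9.5% |
| 20%, 70% | 20%, 70% | 45.0 vs 45.0 | 0 | 5.0% |
| 10%, 70% | 20%, 70% | 47.8 vs 45.0 | −2.8 | 7.3% |

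**Early removal in well patients.** Suppose the rule is read as a total amount, so that early removal also counts as deviation. Add 10% of the drainage arm at an assumed 15% poor outcome to the case f = 20%, q = 70%: p1 = (0.50 − 0.14 − 0.015)/0.70 = 0.493, and the benefit falls to 0.7 points. With 15% such patients, p1 = (0.50 − 0.14 − 0.0225)/0.65 = 0.519, which is 1.9 points against drainage.

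**ITT.** Keeping the excluded patients in the simulated f = 20%, q = 70% case gives a difference of 0.0 points and a rejection rate of 5.7%, which is nominal apart from the discreteness of the uncorrected z-test.

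**The case against.** A reader might infer three stronger things, none of which the document supports.

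*That exclusions fall in one arm only.* They do not: the sentence that sets the 5 ml/h criterion also removes controls who needed a lumbar drain. Only the safety-triggered exclusions are one-sided. The control exclusion has a different and probably narrower trigger, so nothing in the design makes it cancel the other, but it can offset part or all of it.

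*That the per-protocol result must favour drainage.* The table includes null and reversed cases. The rule also catches departures unrelated to severity, such as excess drainage, and may catch early removal in patients who are doing well. High exclusion shares have no support in the text and there are reasons to expect lower ones. Absent or compressed cisterns on the admission CCT already bar entry to both arms, ICP monitoring is mandatory only in sedated, ventilated patients, and the Interventions section leaves the local investigator some discretion over lumbar drainage with compressed cisterns or high ICP. The 36% figure illustrates an unfavourable case and is not an estimate.

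*That per protocol stands equal to ITT and could overturn it.* Nothing calls it co-primary. ITT is listed first, and the power figure uses all 300 patients with no allowance for exclusions, which fits ITT as the basis.

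It is also fair to say that a brief pause may not have been meant as a deviation, and that tolerances are often left to the full protocol or SAP. That covers the missing tolerance. It does not cover a stated exclusion that, as worded, conflicts with stated treatment rules.

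**Conclusion.** The concern holds as an internal contradiction confined to the per-protocol analysis. As worded, the definition classes patients managed according to the protocol's own safety rules as deviators, on post-randomisation events that probably carry prognosis and can exclude only drainage-arm patients.

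The likely direction favours drainage. Against a planned effect of 17 points (50% to 33%), the spurious benefit is a few points under moderate assumptions and about 10 points under severe ones. It disappears if the excluded patients have average prognosis, and it can vanish or reverse with comparable control exclusions or if well patients with early removal also count as deviators. All of this rests on assumed shares and prognoses and on 1:1 allocation.

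The ITT analysis is sound on this point. The false-positive rates would bear on the trial's conclusion only if the per-protocol result were allowed to decide it, which the article neither says nor rules out. Severity: should be fixed.

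**What to change.** Amend the Statistical Analysis section, before outcome data are seen, as follows:

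1. State that ITT (all randomised patients, analysed as randomised) decides the primary question and that per protocol is supportive.
2. Count as adherent any closure, interruption or withholding of drainage that the Interventions section requires.
3. Reconcile the bare 5 ml/h criterion with the approximate rate in the Interventions section by a prespecified tolerance. Reconcile it also with the early-removal and four-day wording in the section on amount and duration, stating whether permitted early removal counts as deviation.
4. Report per-protocol exclusions by arm and by reason.

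The criterion need not be deleted: an exemption and a tolerance are enough, and no further causal analysis is needed. The change concerns analysis sets only and alters no clinical rule. It costs a paragraph of wording and a little programming; the per-protocol result may look less favourable to drainage.
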